### Blood sampling / sample processing / laboratory analysis of cardiac biomarkers

2.7

Blood sampling is performed during clinical routine, whenever possible via the venous central catheter, otherwise via venous puncture. Blood processing to gain study-specific serum and plasma samples are performed as described in the study laboratory manual based on the manufacturer’s instructions. Plasma and serum samples are stored at −80 °C freezers at the respective site. After a maximum storage time of 3 months all samples are shipped on dry ice to the Department of Clinical Chemistry and Laboratory Diagnostics (IKCL − Core Lab) in Jena via a professional laboratory courier service. Cardiac biomarker analysis of TnT, CK, and CK-MB in plasma samples are performed after arrival at the IKCL in Jena according to local routine. The time points of assessment will then allow, for the first time, comparing all three biomarkers and their dynamic and kinetic behaviors with each other. Cardiac biomarker analysis of TnI in serum samples are performed after arrival at the MVZ in Cottbus according to local routine.

### LGE-cMRI / analysis

2.8

For conducting LGE-cMRI study-uniformly a MRI manual has been provided to all participating sites. Myocardial injury will be defined by the presence of abnormalities in T1/T2 mapping, extracellular volume, contractility and/or LGE. The process of mapping provides a quantitative means of objectifying alterations in the myocardium. The extent of left ventricular (LV) enlargement will be measured as a percentage of LV mass. The remaining qualities will be measured according to the AHA-Myocardial Segments classification system. To improve specificity, it will be performed complementary sequences such as T1/T2 mapping and extra cellular measurements to differentiate acute inflammatory changes from chronic scarring. During site initiation and prior to study-specific MRIs each site confirmed that MRI sequencing indicated in the manual is according to local clinical routine. Study-specific MRI data of all participating patients enrolled outside Jena will be transferred to Department of Diagnostic and Interventional Radiology (IDIR – Core Lab) in Jena for central analysis. Data transfer will be performed via TeamBeam, a data protection-compliant data exchange platform for location-independent, encrypted data exchange and for encrypted data storage comprising sensitive data, including email exchange with external partners. The data to be exchanged is password-protected, provided with a validity period, and is automatically deleted from the platform. The analyses will be performed in a blinded core lab (University of Jena) throughout one single investigator in order to reduce intra- and inter-observer variability.

### Possible complications and/or risks

2.9

No additional complications and/or risks for the patients during study participation are expected. Based on the nature of the study and its regulatory classification no safety reporting is required. Nevertheless, for secondary endpoint assessment as well as due to possible study exclusion of patients after enrolment the focus will be on the documentation of the following events:odeath.oMI with angiographic evidence of coronary ischemia.ostroke.opostoperative AV block II° or III° and need for pacemaker implantationore-thoracotomy due to bleeding and/or cardiac tamponade.opostoperative delirium.orespiratory insufficiency with need for re- or protracted invasive ventilationopneumonia.oacute renal failure with indication for dialysis.oallergic reaction to gadolinium (of any degree).operioperative complications resulting in study exclusion (coronary complications, extension of the operation beyond isolated heart valve operation, prolonged extracorporeal circulation e.g ECMO application, resuscitation).

### Statistical considerations and methods

2.10

The statistical approach for the RORSCHACH study is exploratory and essentially descriptive. As mentioned previously, the primary endpoint is the correlation (Spearman's ρ) of the peak value of the respective biomarker (TnI, TnT, CK, CK-MB) with the amount of perioperatively induced myocardial damage quantified by LGE-cMRI. In addition, adequate methods of descriptive statistics to summarize biomarker distributions, exploratory bivariate correlation analyses (Spearman's ρ) and regression modeling (mixed, general linear models) including sensitivity analyses (e.g. stratified by study center) will be performed. There will be no adjustment for type I error.

### Sample Size

2.11

With 85 evaluable patients, who are considered recruitable for practical reasons, α = 0.05 and a power = 0.8 for the primary endpoint H1: ρ = 0 against H0: ρ = 0.3 can be detected. Assuming a drop-out rate of 15 %, the required number of patients to be included is 100.

### Interim analysis

2.12

There will be no interim analysis.

### Methods against bias

2.13

All participating sites are certified cardiothoracic centers and have a quality management system. Investigators have to be trained in good clinical practice (GCP). All surgeons should be qualified cardiac surgeons and hold the appropriate national diploma or at least operate under surveillance of a senior cardiac surgeon. At each visit the occurrence of possible outcomes will be documented in the case report form (CRF).

Ultimately, patients who experience definitive intraoperative shock necessitating resuscitation doses or comparable interventions will be included in separated analyses. Intraoperative shock will be defined as any of: sustained hypotension (MAP < 40 mmHg ≥ 20 min), sustained high-dose vasopressors (norepinephrine ≥ 0.10 µg/kg/min, epinephrine ≥ 0.05 µg/kg/min, vasopressin ≥ 0.03 U/min, or ≥ 2 concurrent agents for ≥ 10 min), resuscitation interventions (CPR/defibrillation; push-dose vasopressor rescue ≥ 100 µg epinephrine or ≥ 400 µg phenylephrine within 10 min; massive transfusion ≥ 4 PRBC/60 min), or metabolic/oxygenation evidence of shock.

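### Resuscitated patients are both excluded from the study and kept for separate analysis, so the set for the primary correlation cannot be determined from the text

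*Protocol article*

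**What the plan says.** The protocol article handles these patients in two ways.

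**Out of the study.** Section 2.3.2 lists, as an exclusion criterion, perioperative complications capable of causing myocardial damage. Table 1 in section 2.6 checks for such complications at every time point from 0 h to 120 h and attaches an immediate end of participation. Section 2.9 names the events concerned: "complications resulting in study exclusion (coronary complications, extension of the operation beyond isolated heart valve operation, prolonged extracorporeal circulation e.g ECMO application, resuscitation".

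**In, and analysed apart.** Section 2.13 says that "patients who experience definitive intraoperative shock necessitating resuscitation doses or comparable interventions will be included in separated analyses". Shock is met by any one of several items, and CPR or defibrillation is among them. The last item is "or metabolic/oxygenation evidence of shock", without a limit. The Discussion (section 3) repeats the plan. Its reason is that severe hypotension or high-dose vasopressors may injure the myocardium independently of the operation.

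**Primary endpoint and size.** Section 2.10 states that "the primary endpoint is the correlation (Spearman's ρ) of the peak value of the respective biomarker" with new damage on LGE-cMRI. Section 2.11 starts "With 85 evaluable patients, who are considered recruitable for practical reasons", gives "α = 0.05 and a power = 0.8 for the primary endpoint", and ends "Assuming a drop-out rate of 15 %, the required number of patients to be included is 100". It does not say what counts as drop-out.

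**The concern.** A patient who needs CPR during valve surgery meets both rules. Under sections 2.3.2, 2.6 and 2.9 that patient's study ends at once. Under section 2.13 the patient contributes to an analysis.

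The choice matters because the primary endpoint correlates peak biomarker with new damage, and these patients have a recognised cause of damage. Whether they are in or out affects the range of both variables. Removing them plausibly narrows that range and pulls ρ towards zero, although the documents give nothing from which to size this. Sites that follow different sections would supply different patients to the primary correlation.

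It also matters for the sample size, since the text does not say whether a further group may be taken out of the 85 evaluable patients.

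**Working it through.** **1. The rules side by side**

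| Question | Sections 2.3.2, 2.6 (Table 1), 2.9 | Sections 2.13, 3 |
|---|---|---|
| Resuscitation | leads to study exclusion | CPR/defibrillation is a shock item; patient analysed separately |
| Hypotension, high-dose vasopressors | not named; covered by 2.3.2 if they may cause myocardial damage, which section 3 says they can | shock items; patient analysed separately |
| Postoperative LGE-cMRI | not reached if participation ends before 120 h | needed for any biomarker–damage correlation |

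Reading section 2.9 as postoperative only does not remove the clash. Its list is headed perioperative and contains an event that can only be intraoperative, the extension of the operation. The explicit conflict concerns resuscitation. For the other shock items it follows from reading section 2.3.2 together with section 3.

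**2. Reproducing the planned size**

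Inputs from section 2.11: α = 0.05, power 0.80, ρ = 0.3 against 0, drop-out 15%. Sidedness is not stated; a two-sided test reproduces the figure. The hypothesis labels are interchanged in the text ("H1: ρ = 0 against H0: ρ = 0.3 can be detected"); here the null is taken as ρ = 0.

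Fisher z: n = [(z₀.₉₇₅ + z₀.₈₀) / atanh(0.3)]² + 3 = [(1.960 + 0.842) / 0.3095]² + 3 = 84.93, so 85.

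Enrolment: 85 / 0.85 = 100. Both stated figures reproduce.

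**3. Reserve**

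Power = Φ(atanh(0.3) × √(n − 3) − 1.960).

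- n = 85: Φ(0.3095 × √82 − 1.960) = 0.8003
- n = 84: 0.7955

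The first patient lost beyond the 15% takes power below 0.80.

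**4. If shock patients leave the primary analysis in addition to the 15%**

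The documents give no shock rate, so the shares below are assumptions. Remaining n is 85 × (1 − share), to the nearest whole patient with halves rounded down. Enrolment to keep 85 is 85 / [0.85 × (1 − share)], rounded up.

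| Assumed share removed | n in primary analysis | Power at ρ = 0.3 | Enrolment to keep 85 |
|---|---|---|---|
| 0% | 85 | 0.800 | 100 |
| 5% | 81 | 0.780 | 106 |
| 10% | 76 | 0.753 | 112 |
| 20% | 68 | 0.704 | 125 |
| 30% | 59 | 0.639 | 143 |

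These figures hold ρ at 0.3 and include no attenuation from a narrower range.

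**5. If they stay in the primary analysis, or the 15% already covers them**

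n = 85 and power = 0.80, as planned.

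**The case against.** **Separate may mean additional.** Section 2.13 can be read as an extra analysis that leaves the primary set untouched. Section 2.9 foresees exclusion after enrolment, and drop-out is undefined, so the 15% can also be read as covering these losses. Both readings are open. A reader might infer that the trial will fall short of its 85 patients. The documents do not support that as a fact, because it would require removal from the primary set, removal in addition to the 15%, and a shock rate that is not given.

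**Data collected before exclusion could still be described.** This is correct, and a purely descriptive separate analysis is possible. A correlation with new damage is not possible without the second MRI.

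**The study is exploratory.** Section 2.10 calls the approach exploratory and mainly descriptive, and section 2.11 ties the 85 to practical recruitability. A conditional loss of power therefore carries less weight. This argues for a lower severity but does not answer the clash of rules.

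**Sites steering patients.** The study is unblinded and the last shock item has no limit, so a reader might infer that sites could move patients out in the light of results. The text does not bear this out. Study biomarkers are measured centrally from frozen samples (section 2.7), the MRI is read in a blinded core lab (section 2.8), and intraoperative shock precedes every postoperative measurement. What remains is that the article does not say who classifies shock, or when. The missing limit is a minor point, since a fuller document may supply it.

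**The separation is deliberate.** The Discussion gives a confounding rationale for setting these patients apart. That is a legitimate choice of target population, so it does not follow that they must be in the primary correlation.

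**Conclusion.** The contradiction stands. Resuscitated patients are excluded with an immediate end of participation in one group of sections and kept for analysis in another, and the section 2.3.2 wording extends the doubt to the wider shock group. Because these are stated rules that clash, the brevity of a journal article does not explain it. The primary correlation set cannot be determined from the text.

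The consequence for power is conditional: from 0.78 at an assumed 5% removal to 0.64 at 30% if these patients come off on top of the drop-out, and no change from 0.80 otherwise. It rests on a two-sided Fisher z calculation with ρ = 0.3. Attenuation of ρ is plausible but not quantified. In an exploratory study this is something that should be fixed before analysis, not a fatal flaw.

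**What to change.** 1. Reconcile sections 2.3.2, 2.6 (Table 1), 2.9, 2.13 and 3 to one rule for patients with resuscitation or intraoperative shock. Which rule is for the investigators to decide.
2. State which patients form the primary Spearman correlation, and whether the 15% covers those excluded or analysed separately.
3. Report the correlation with and without shock patients who have both MRIs, as a sensitivity analysis.
4. Tie the last shock item to recorded values, and classify shock from intraoperative records without sight of biomarker or MRI results.
5. If these patients are removed from the primary set in addition to the drop-out, restate the power for the reduced number.

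The cost is protocol wording and one added analysis. If step 5 applies, the stated power becomes less favourable.

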### Ethical considerations

2.14

Approval for the study was obtained by the leading ethics committee of the Friedrich Schiller University Jena (no. 2022–2559-BO). In addition, and insofar necessary according to local regulations, the responsible ethics committees of participating sites approved the study protocol before conducting any study-specific measures.

### Data management

2.15

Data acquisition will be done via web application into the study management software OpenClinica®. The software meets the regulatory requirements (GCP, 21CFR Part11). The data will be entered via encrypted connection (https) in web browser input masks. Each subject will be given an unambiguous patient identification number (subject ID) to ensure pseudonymized data analysis.

### Privacy, collection and processing of data

2.16

The data obtained in the course of the study will be treated pursuant to the appropriate Data Protection Law. During the study, subjects will be identified solely by an individual patient identification number (subject ID). Study findings stored on a computer/server will be stored in accordance with local data protection law and will be handled in strictest confidence.

### Study Status

2.17

The RORSCHACH study started recruiting in September 2023. Recruitment is planned to be completed by September 2025.

### Dissemination

2.18

The results of this study will be published in a renowned international medical journal, irrespective of the outcomes of the study.

## Discussion

3

The RORSCHACH trial will deliver the first comparative and quantitative information on the predictive value of the three classic cardiac injury markers used for the detection of new perioperative irreversible injury/MI in cardiac surgery.

Cardiac biomarkers are essential tools for diagnosing perioperative MI, yet their specificity remains contentious. We had discussed the inadequacy of defining MI solely based on biomarkers before [3]. A thorough comparison between different biomarkers after cardiac surgery and the quantitative relation to myocardial damage is lacking. The topic has raised substantial attention with several prominent publications [[6], [7], [8]] attempting to define cut-off values for the detection of MI by biomarker release only. While it is clear, that every true MI will cause the release of the proteins used for MI detection (specifically if it is a larger infarction), at low to intermediate amounts of biomarker release, it is not clear which pathophysiology is associated with the release observation. Since these intermediate values are most frequent, it is important to provide clarity, especially since MI definitions based on biomarker release only have been and still are used [[6], [7], [8]] for determining trial endpoints, in which surgery is compared to less invasive treatment modalities. Since biomarker release may also be associated with surgical stress, without being directly related to myocardial injury, this possibility may introduce a significant bias into the interpretation of trial results.

Although CAD patients were excluded, intraoperative factors such as severe hypotension or high-dose vasopressor use could lead to myocardial injury independent of the surgical procedure, which are residual confounders which can be hardly addressed quantitatively. For this reason, patients who develop clear cases of intraoperative shock requiring resuscitation doses or similar interventions will be subject to separated analyses.

With RORSCHACH, we are going to deliver the first comparative and qualitative information on the predictive value of the classic cardiac biomarkers for the detection of new perioperative irreversible injury/MI in the heart surgery setting. Demonstrating this laboratory and radiological correlation would be one of the first evidence-based steps forward in optimizing the diagnosis of truly significant clinical events in patients after cardiac surgery. This trial will generate important information with significant implications for not only daily practice but importantly for the design of new clinical trials involving coronary artery disease.

## Patient and public Involvement

7

Patients and/or the public were not involved in the design, or conduct, or reporting, or dissemination plans of this research.

## Patient consent for Publication

8

Not required.

## Data Availability

The data underlying this article will be kept digital and on file for the next 10 years.
